#### 2.3.2. Exclusion Criteria

Sensory or motor limitations that prevent the use of electronic devices (computer, tablet, or mobile phone) reported by caregivers or pediatriciansPhotosensitive epilepsy, reported by pediatricians.Uncontrolled aggressive behavior, reported by local Specialized Educational Guidance Team for Severe Behavioral Disorders or pediatricians

### 2.4. Intervention

#### 2.4.1. Overview and Theoretical Basis

DiverAcción is a digital telerehabilitation system designed to train executive skills—planning, organization, and time management—and emotional self-regulation in virtual contexts with high ecological validity (Table 1; Figure 1). The program is grounded in organizational skills training for children with ADHD, adapted to interactive digital environments [26,33], and in Adele Diamond’s model of executive functions [6].

The intervention emphasizes planning and organization, acknowledging a non-linear EF trajectory with rapid gains at 10–15, decelerating improvement at 15–18, and stabilization toward 18–20 [3]; complex planning can continue improving into the late teens/early twenties [4]. Planning matures later than working memory and inhibition [5]. The design also incorporates the development of prospective memory (PM)—event-based vs. time-based demands—and its reliance on executive control [8,9,34].

#### 2.4.2. Components of the Intervention

The intervention comprises two core dimensions: (1) Collaborative agenda, and (2) Training. The collaborative scheduling component is co-designed with participants to improve and apply planning, organizational, and time management skills in daily life. It is intended for daily use to establish a routine of planning and monitoring activity completion. In parallel, each participant will complete twelve 45-min virtual training sessions, delivered twice per week across six weeks. Training activities are gamified to enhance motivation while targeting planning, organization, time management, and emotional self-regulation.

#### 2.4.3. Child-Centered, Metacognition-Supportive Agenda

The program will be child-centered: each participant will construct a personal agenda that aligns training tasks with daily routines and demands. The agenda will function as a metacognitive scaffold (plan–monitor–evaluate), nurturing planning and self-regulation [35,36]. Evidence indicates that metacognitive skills are trainable in school settings and uniquely contribute to performance beyond intellectual ability [37,38].

#### 2.4.4. Delivery Format and Dosage

The program will be delivered entirely in a digital, remote format over six weeks. Participants will engage in scheduled online training activities, utilize the digital agenda for planning and organization, and attend synchronous videoconference sessions led by trained occupational therapists. The six-week protocol comprises 12 child/adolescent sessions (two per week) and six parent/teacher sessions (one per week), aligning with the dosage planned for the subsequent randomized controlled trial. In addition to scheduled sessions, participants will be instructed to use the collaborative agenda daily (seven days per week) throughout the intervention to support continuous engagement and transfer of strategies to natural home–school contexts.

#### 2.4.5. Developmental Adaptations (EF, ER, PM)

Implementation was scaled to age-related EF capacities and emotion-regulation needs, grounded in contemporary neurodevelopmental models [6] and adolescent emotion circuitry [7]. his age-adjustment approach is consistent with prior interventions targeting planning and organization, which tailor content with age-appropriate task sets (e.g., one set for 6–9 and another for 10–13 years) [39]. In our study, participants will be grouped into three bands (9–11, 12–14, 15–17) to align task demands with developmental stages of EF, ER, and PM [9,34]: (a) 9–11 years: Greater reliance on external scaffolds, salient event cues, and guided time monitoring; event-based PM benefits from cues, whereas time-based PM requires more self-initiated monitoring [8,11]; (b) 12–14 years: Increased emotional reactivity with emerging, inconsistent self-initiated control; tasks emphasized structured monitoring, graded autonomy, and explicit ER supports [7,40]; (c) 15–17 years: More advanced planning and prospective organization, but vulnerability under high cognitive/emotional load and complex PM paradigms; encouraged self-monitoring, anticipatory planning, cognitive reappraisal, and autonomous compensatory tools (e.g., digital reminders for time-based PM) [34,41]. In ADHD, PM shows uneven trajectories and deficits—often more pronounced for time-based PM due to higher monitoring demands—and ER difficulties are common; strengthening working memory and monitoring may indirectly benefit ER and PM [10,42,43].

#### 2.4.6. Caregiver Psychoeducation Component

To support generalization and caregiver mediation, the weekly psychoeducation for parents/teachers will follow established occupational therapy models. Specifically, Cog-Fun and POET typically deliver 6–10 weekly sessions and have demonstrated improvements in parental self-efficacy, adherence, and child functioning/participation, with effects maintained at follow-up in school-age samples [17,19,20,44]. Accordingly, the six-session parent/teacher component will be adopted to maximize transfer and contextualization of child strategies in daily routines. Given this dosing, three-month results should be interpreted with caution, and future research may evaluate protocols with a greater number of sessions or longer follow-up to determine the sustainability of effects.

#### 2.4.7. Session Structure and Rationale for Duration

Each session will last approximately 45 min, a duration selected to allow coverage of multiple cognitive tasks and metacognitive strategies within a single block, thereby supporting the repeated practice necessary for executive function training. This time frame is consistent with prior digital ADHD interventions [45,46] and comparable to traditional occupational therapy programs such as POET and Cog-Fun [16,19]. The session structure incorporates short activity segments and gamified elements with immediate feedback to maintain attention and motivation.

#### 2.4.8. Participant Support and Supervision

Throughout the intervention, participants will have the support of an assigned therapist from the research team, available to address questions or issues via the application’s internal chat or email (for children/adolescents and legal guardians). In addition, two supervisory videoconferences will be scheduled—Week 1 and Week 3—to answer questions and assess progress. If necessary, users or guardians may request additional videoconferences via chat or email, which will be scheduled according to the availability of the research team and families.

#### 2.4.9. Digital Capture and Usage Metrics

The platform will automatically record number of completed tasks, tasks initiated but not finished, tasks not initiated, duration of activities, average session duration, and active usage rate.

#### 2.4.10. Therapist Training

To ensure standardized delivery, all occupational therapists administering the intervention will complete a 20-h training program before implementation. This program covers theoretical foundations, intervention procedures, and the use of digital tools, including protocols for remote engagement and troubleshooting in virtual environments.

#### 2.4.11. Fidelity Assurance Procedures

Treatment fidelity will be maintained through a structured process that includes session checklists completed online by clinicians after each session to confirm adherence to prescribed components and session objectives; weekly remote supervision meetings with the principal investigator to provide feedback and address protocol-adherence issues; and ongoing digital support for technical or procedural queries. Fidelity will be monitored and reported as part of the feasibility outcomes (see Statistical Analysis for details on measurement, thresholds, and inter-rater verification).

#### 2.4.12. Rationale for Six-Week Duration

The selected six-week duration is consistent with recent digital ADHD interventions showing that multi-week, multi-session protocols (including four-week cycles) are feasible, achieve high adherence, and can yield preliminary functional improvements—for example, a 4-week digital therapeutic with high session compliance and attentional gains in 8–12-year-olds [45], and a 4-week RCT delivering 12 sessions (3/week; 30 min) with acceptable retention (~89%) and improvements in parent-rated symptoms and executive function [46]. At the same time, the field has not established a definitive “optimal dosage” for digital ADHD interventions; systematic reviews will be considered when interpreting dose–response heterogeneity [47,48].

### 2.5. Adverse Event Monitoring and Reporting

Although the intervention is considered low risk, the protocol includes systematic monitoring of adverse events to ensure participant safety. Low-risk events may include mild fatigue, frustration, emotional discomfort, headache, eye strain, or transient anxiety during tasks. These events will be documented in an adverse event log and managed by pausing the session, providing reassurance, and adjusting task demands as needed.

Serious adverse events (SAE) are defined as any event resulting in hospitalization, significant disability, life-threatening condition, or severe psychological reaction (e.g., acute anxiety crisis or suicidal ideation). Although SAE are highly unlikely in this context, the protocol specifies that any such event will trigger immediate suspension of the intervention, provision of appropriate support, and notification of the principal investigator and the institutional ethics committee within 24 h.

Participants and caregivers will receive written and verbal instructions on how to report any adverse events during or after sessions. The research team will maintain a standardized log documenting the nature, severity, and resolution of each event. The absence or presence of adverse events will be summarized in the final feasibility report.

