#### 2.9.4. Contextual Variables: Concomitant Care, Medication, and External Events

Concurrent services (type, frequency, dosage) will be documented at baseline and weekly; ADHD medication regimen (drug, dose, schedule) and any changes will be recorded weekly for applicable participants. School calendar events and major life changes will be logged to contextualize adherence and outcomes. Analyses will include sensitivity checks stratifying by concomitant care intensity and medication stability (stable vs. changed).

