User-friendly design	Visual analog scale from 1 to 10	T1	Children and Adolescents Parents Teacher Occupational Therapists
Participant satisfaction	Participant Satisfaction Questionnaire	T1	Children and Adolescents Parents Teacher Occupational Therapists
Therapeutic Alliance	WAI-I	T1	Children and Adolescents
Executive functioning	BRIEF-2 for parents and teachers TEXI Inventory	T0, T1, T2	Parents and Teachers Children and Adolescents
Time management of children and adolescents	Time-S questionnaire EMT	T0, T1, T2	Children and Adolescents Teachers
Prospective Memory	PRMQ-C Automated metrics recorded by the platform	T0, T1, T2 T1	Children and Adolescents
Emotion regulation strategies in everyday life	ERQ-CA	T0, T1, T2	Children and Adolescents
Health-related quality of life (HRQoL)	KIDSCREEN-52	T0, T1, T2	Children and Adolescents
Parents’ perceptions of their parenting competence	BPSES	T0, T1, T2	Parents
Parental stress levels	PSI-4-SF	T0, T1, T2	Parents

Note: T0 = baseline, T1 = immediately post-intervention, T2 = 3 months after intervention.

**Table 3 healthcare-14-00323-t003:** Progression Criteria for Feasibility Outcomes.

Domain	GO (Proceed)	AMEND (Modify)	STOP (Do Not Proceed)
Recruitment	≥70% of eligible approached	50–59%	<50%
Retention	≥80% at T1/T2	60–79%	<60%
Data completeness	≥80% completeness	70–79%	<70%
Adherence	≥80% agenda & training; 100% videoconferences	60–79% agenda/training	<60% agenda/training
Fidelity	≥80% protocol elements delivered	60–79%	<60%
Acceptability (TAM)	Mean ≥ 3.5	Mean 3.0–3.49	Mean < 3.0
Usability (SUS)	Score ≥ 68	Score 60–67	Score < 60
Dropouts	≤20% dropout rate	21–29% dropout rate	≥30% dropout rate

Note. GO = criteria met for progression to definitive trial; AMEND = criteria met with modifications; STOP = criteria not met. Predefined success thresholds were based on widely used benchmarks in feasibility research, such as ≥80% session completion [69], SUS ≥ 68 [55], and TAM mean ≥ 3.5 [70].

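### Adverse-event monitoring is called systematic, but no scheduled enquiry, baseline symptom value or collection period is described, so a report of no events would be weak evidence of tolerability

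*Protocol article*

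**What the plan says.** Section 2.5 states that "the protocol includes systematic monitoring of adverse events to ensure participant safety". It lists the mild events it expects: fatigue, frustration, emotional discomfort, headache, eye strain and transient anxiety. For these it says: "These events will be documented in an adverse event log and managed by pausing the session, providing reassurance, and adjusting task demands as needed". It defines serious events and requires notification within 24 hours.

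On how events become known, the section says: "Participants and caregivers will receive written and verbal instructions on how to report any adverse events during or after sessions". On recording: "The research team will maintain a standardized log documenting the nature, severity, and resolution of each event". On output: "The absence or presence of adverse events will be summarized in the final feasibility report".

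Other parts of the article bear on this:

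- Section 2.4.8: "Throughout the intervention, participants will have the support of an assigned therapist from the research team", by chat or email, with two scheduled videoconferences in weeks 1 and 3.
- Section 2.4.11: clinicians complete an online checklist after each session, for fidelity.
- Section 2.9.4: concurrent services are documented at baseline and weekly. For ADHD medication, the regimen and "any changes will be recorded weekly for applicable participants".
- Table 2 assigns instruments to time points, with the note "T0 = baseline, T1 = immediately post-intervention, T2 = 3 months after intervention". It has no adverse-event row.

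**The concern.** A log stores events once someone knows of them; it does not find them. Whether monitoring is systematic depends on whether the same question is put to every child at set times, and the article describes no such question. The events most likely here are mild and common, and families may not think to report a headache or tired eyes unless asked.

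Two further gaps weaken the summary. First, the named symptoms are not measured at T0. Section 2.1 says there is no control group, and section 2.9.4 shows that some children will be on ADHD medication. A logged headache therefore cannot be separated from one that was there before or has another cause. Second, the article fixes no end date for collection, although children are seen again at T2.

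What is at stake is the safety information carried forward to the planned randomised trial in minors. If the report says that no events occurred, its readers cannot tell whether there were none or whether few were asked about.

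**Working it through.** The plan gives no adverse-event rate, and its sample of 30 rests on no power calculation (section 2.7), so there is no figure of its own to reproduce. The check has a textual part and an illustration.

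**Textual part: each contact or record, and whether adverse events are named there**

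- Instructions to participants and caregivers (2.5): yes, family-initiated, with no end date.
- In-session management and log (2.5): yes. Pausing a session implies that staff can become aware of an event while it runs.
- Remote supervision of sessions (2.2, 2.6): adverse events not named, and the extent of live observation is not stated.
- Chat and email (2.4.8): offered for questions or issues, adverse events not named.
- Videoconferences in weeks 1 and 3 (2.4.8): for questions and progress, adverse events not named.
- Clinician session checklist (2.4.11): for components and objectives, adverse events not named.
- Automated platform metrics (2.4.9): tasks, durations and usage only.
- Weekly record of medication and concurrent care (2.9.4): adverse events not named.
- Assessments at T0, T1 and T2 (2.6, Table 2): no adverse-event item.

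So there are two described sources, family reports and what staff happen to notice in a session. Neither is a scheduled enquiry.

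**Illustration: what zero recorded events would exclude**

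Inputs: n = 30 from section 2.7. Let s be the share of affected children who get recorded. The documents do not give s, so it is assumed and varied from 100% to 25%.

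With zero recorded events, the one-sided 95% upper bound on the recorded rate is 1 − 0.05^(1/n). For n = 30 this is 1 − 0.05^(1/30) = 9.5% (the two-sided exact bound is 11.6%). The recorded rate is s times the true rate, so the bound on the true rate is 9.5% / s:

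- s = 100%: 9.5%
- s = 75%: 12.7%
- s = 50%: 19.0%
- s = 25%: 38.0%

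If only 24 children are observed (80% of 30, the GO level for retention in Table 3), the bound with full capture is 1 − 0.05^(1/24) = 11.7%.

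The chance of recording nobody with a given symptom, at an assumed true risk p per child, is (1 − p·s)^30:

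- p = 20%: 0.1% at s = 100%, 4.2% at 50%, 21.5% at 25%
- p = 10%: 4.2% at s = 100%, 21.5% at 50%, 46.8% at 25%

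For a symptom that truly affects one child in ten, an empty record is unlikely when everyone is asked. It occurs about one time in five when half of the affected children are recorded.

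**The case against.** The strongest reply is that this is a journal article. An elicitation form and a collection period could sit in a fuller protocol that is not shown, and their absence alone would not be a finding. That has force. The article does give a log and its fields, a definition of serious events and a notification time. The point survives because section 2.5 makes a positive claim of systematic monitoring, describes a passive method, and plans to report absence on that basis.

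A second reply is that Table 2 is not a complete schedule. The weekly medication record, the fidelity checklists and the life-event log have no row for their collection during the intervention either. This is fair: the missing row proves little alone. But those other records are described in the text as actively collected, and an adverse-event enquiry is not.

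Third, adverse events are not a progression criterion in Table 3, so no GO, AMEND or STOP decision changes. This stands, and it limits the severity.

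Three stronger readings are tempting, and the documents do not support them:

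- A reader might infer that reporting stops at week 6. No section says so. Section 2.4.8 limits therapist chat and email support to the intervention and does not name it as the adverse-event channel. The instruction in 2.5 covers the time after sessions and has no end date. For the same reason one cannot say that the months from T1 to T2 have no channel, only that none is specified.
- A reader might infer that an event is captured only if a family volunteers it. Sessions are remotely supervised, and in-session pausing and logging imply that staff can record what they see.
- A reader might conclude that a report of no events would be worthless. The capture shares are assumptions. At a 20% risk and 50% capture, the chance of recording none for one symptom is only 4.2%.

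**Conclusion.** The point holds as a mismatch between label and method. The article promises systematic monitoring, but it describes family-initiated reporting plus incidental observation by therapists. It gives no scheduled enquiry, no baseline symptom value and no stated collection period.

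A statement of absence would be weak evidence of tolerability. Even with full capture, 0 of 30 leaves rates up to 9.5% open. With an assumed 50% capture it leaves rates up to about 19% open. The first figure needs only n = 30 and independent children; the second also rests on the assumed capture share.

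Severity is minor to moderate. Confidence is medium, because a fuller protocol may hold some of the missing detail.

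**What to change.** Add one adverse-event row to Table 2 and a matching sentence in section 2.5:

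1. Use one short checklist of the mild symptoms already named in 2.5, plus one open question. Ask it at T0 (for symptoms already present), with the weekly medication and concurrent-care record of section 2.9.4, at T1 and at T2.
2. State that collection runs to T2, and name the channel families use between T1 and T2.
3. Report solicited and spontaneous events separately, each as the number of children with at least one event that is new or worse than at T0, out of all children who started.
4. If no event of a kind is recorded, give the upper confidence bound with the zero.

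The cost is a few minutes at contacts that already exist. Asking will also turn up more mild events, so the safety summary will look somewhat less favourable than one built on spontaneous reports.

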### 2.6. Timelines and Schedule

After participant selection, an initial in-person session will be held with the participants and their legal guardians. During this session, instructions for starting the study, information on how to use the DiverAcción platform, available communication channels, and data security measures will be provided. Initial data collection (baseline, T0) will also take place during this session.

Training sessions will be conducted over the following six weeks, entirely online and under the remote supervision of the research team’s therapists. Once the twelve sessions are completed, a second in-person data collection session (post-intervention, T1) will be held during the same week the intervention ends.

Finally, a third evaluation (follow-up, T2) will be conducted three months after the intervention ends to assess the maintenance of the effects and long-term adherence. The three-month follow-up interval was chosen based on prior research on executive function interventions in children and adolescents with ADHD, where short- to medium-term maintenance of effects is commonly assessed within a 3–6-month window. This timeframe is considered sufficient to detect initial trends in maintenance or potential decay of intervention benefits while balancing feasibility and participant burden in a feasibility study. Previous studies have reported sustained improvements in working memory, attention, and processing speed at three-month follow-up after cognitive or combined interventions [39,49,50]. Therefore, the three-month interval aligns with established practices and provides meaningful preliminary data on the durability of intervention effects.

Therefore, data collection will take place at three points in time:Baseline (T0): before the start of the intervention.Post-intervention (T1): immediately after the twelve sessions.Follow-up (T2): three months later.

All in-person sessions will be held in a classroom at the local University. The flowchart in Figure 1 shows the timeline of the different phases of the study.

### 2.7. Sample Size

The planned sample size is 30 children/adolescents. This number is considered adequate for feasibility and usability studies in children and adolescents [25,51], ensuring sufficient variability to identify barriers and facilitators without requiring a formal calculation of statistical power [52]. This study was designed as a pilot trial aimed at assessing the feasibility and acceptability of the intervention. The sample size (n = 30) is considered appropriate for feasibility objectives, as it allows for the evaluation of implementation aspects, adherence, usability, acceptability and participant satisfaction. However, this sample size is insufficient to establish the efficacy of the intervention; Therefore, the findings should be interpreted as preliminary and intended to inform the design of future randomized controlled trials with larger samples.

